**Questionnaires**				
	**Pain**			
		Severity of pain: VAS^a^ [20]	The scale ranges from 0 to 100, where 0 indicates no pain at all and 100 indicates the worst possible pain.	
		Neuropathic pain: painDETECT [21]	The screening questionnaire identifies neuropathic components in patients with pain.	
		Fear of movement: TSK^b^ [22]	The screening questionnaire detects fear of movement due to pain.	
		OKS^c^ [24,25]	The 12-item questionnaire assesses knee pain and functionality.	
		WOMAC^d^ [26]	The disease-specific questionnaire explores the effects of osteoarthritis treatment intervention.	
	**Quality of life**			
		RAND-36^e^ [23]	The questionnaire explores well-being and functional ability across eight dimensions: general health perceptions, physical functioning, emotional well-being, social functioning, energy, bodily pain, role functioning/physical, and role functioning/emotional.	
	**Depression and anxiety**			
		BDI-21^f^ [27]	The 21-item questionnaire measures depression.	
		STAI^g^ [28]	The 40-item questionnaire measures trait and state anxiety.	
**Functional tests**				
	Knee ROM^h^ in degrees (°) [29]		Knee ROM (flexion and extension) is measured using a goniometer.	
	Knee swelling (cm) [30]		Knee joint swelling is measured using a tape measure at the popliteal.	
	Thigh circumference (cm) [31]		The thigh circumference is measured using a tape measure 15 cm above the upper edge of the patella.	
	Single-leg stance (s) [32]		The balance test assesses static balance and upright posture control on a support surface narrower than a normal stance.	
	TUG^i^ (s) [33,34]		The functional test measures an individual’s mobility/ability to move.	
	Stair climbing test (s) [35]		The functional test measures the functionality of the lower extremities and balance control. Here, the test was systematically conducted on the same staircase, which had 11 steps. The depth of one step was 34 cm, and the height was 14.5 cm.	
	6MWT^j^ (m) [36]		The functional test measures an individual’s endurance and walking ability.	

^a^VAS: visual analogue scale.

^b^TSK: Tampa Scale of Kinesiophobia.

^c^OKS: Oxford Knee Score.

^d^WOMAC: Western Ontario and McMaster Universities Osteoarthritis Index.

^e^RAND-36: RAND 36-item Health Survey 1.0.

^f^BDI-21: Beck Depression Inventory.

^g^STAI: State-Trait Anxiety Inventory.

^h^ROM: range of motion.

^i^TUG: Timed Up and Go test.

^j^6MWT: 6-minute walk test.

**Table 2 table2:** Patient schedule of enrollment, interventions, and assessments.

			Enrollment		Study period															
					Initial assessment		Allocation		Post-allocation											Closeout
			–2 to –3 weeks		–1 to –2 weeks		0 weeks		3-6 weeks		6-8 weeks		4 months		6 months		12 months		12 months	
**Enrollment**																				
	Eligibility screen	✓																		
	Informed consent	✓																		
	Allocation					✓														
**Interventions**																				
	Intervention (AlterG)							✓^a,b^		✓^b^										
	Control group (traditional exercises)							✓^b^		✓^b^										
**Assessments**																				
	Questionnaires (VAS^c^, PainDETECT, TSK^d^, RAND-36^e^, OKS^f^, WOMAC^g^, BDI-21^h^, and STAI^i^)			✓						✓		✓				✓		✓		
	Functional tests (ROM^j^, knee swelling, thigh circumference, single-leg stance, stair climbing test, and 6MWT^k^)			✓								✓				✓		✓		
	6-month questionnaire													✓						

^a^AlterG training (10 times).

^b^Traditional home exercises that the patient was instructed to perform in the hospital after the total knee arthroplasty.

^c^VAS: visual analogue scale.

^d^TSK: Tampa Scale of Kinesiophobia.

^e^RAND-36: RAND 36-item Health Survey 1.0.

^f^OKS: Oxford Knee Score.

^g^WOMAC: Western Ontario and McMaster Universities Osteoarthritis Index.

^h^BDI-21: Beck Depression Inventory.

^i^STAI: State-Trait Anxiety Inventory.

^j^ROM: range of motion.

^k^6MWT: 6-minute walk test.

**Figure 1 figure1:**
[figure not shown]
Study procedure.

### Postoperative Exercises

Furthermore, all the patients (intervention and control groups) in the study independently performed the postoperative exercises instructed by the hospital’s physiotherapists. The exercises were aimed to improve knee ROM and quadriceps and hamstring muscle strength and to stimulate venous circulation. Patients also received guidance on walking with crutches. They were instructed to perform home exercises for approximately 2 months after surgery. However, the researchers do not have information on how actively the patients were engaged with home exercises. The home exercises are described in Table 3.

**Table 3 table3:** Traditional home exercises.

Exercise	Description	Aim
Knee flexion (sitting/supine position)	Sitting on a chair or in the supine position, the patient flexes the knee as much as possible, sliding the sole of the foot backward on the ground. The patient keeps the knee flexed for a while and then returns the lower limb to the starting position, sliding the sole of the foot forward.	To increase knee mobility in the direction of flexion
Knee flexion (standing position)	In the standing position, the patient brings the operated foot on a stair and shifts the weight forward, stretching the knee in the direction of flexion.	To increase knee mobility in the direction of flexion
Quadriceps strengthening (sitting/supine position)	In the sitting or supine position on a bed, the patient extends the knee and presses it against the platform or a towel roll by activating the quadriceps muscles. When performing this in the supine position, at the end of the movement, the patient can lift the straight leg off the ground. Quadriceps strengthening can also be done by sitting on a chair and lifting the straight leg off the ground.	To activate and strengthen the quadriceps muscles and the end-extension of the knee
Ankle pump movements (flexion and extension)	In the supine position, the patient flexes and extends the ankles in turns.	To stimulate and enhance venous blood circulation
Dynamic calf stretching	In the standing position, the patient performs a dynamic calf stretch, taking a step backward with the operated leg and pressing the heel on the ground while extending the knee and then lifting the heel off the ground and letting the knee flex.	To stretch the calf muscles
Hamstring stretching	In the sitting position and with the operated leg straight on the bed, the patient bends the upper body forward and stretches the hamstring muscles.	To stretch the hamstring muscles
Toe raises	In the standing position, the patient takes support from the back of the chair with their hands and rises to their toes and then returns to the starting position.	To activate the calf muscles
Walking with crutches	The patient is instructed on how to walk with crutches after the surgery, using either three-point walking or alternating walking, or with only one crutch. The patient is also instructed to walk on stairs with a crutch/crutches.	To guide the patient on how to use crutches after the surgery

### Outcome Assessment and Measurements

The primary outcomes were walking ability measured with the 6MWT, health-related QoL measured with RAND-36, and perceived pain measured with VAS. All outcomes were measured before the TKA and 4 and 12 months after the TKA. In addition to this, the patients were asked to complete the same questionnaires 6-8 weeks after the TKA. The initial measurements were performed 1-2 weeks before the TKA. Depending on the patient, it took a total of 1.5-2 hours to complete the questionnaires and execute the functional tests. The same measurements were performed 4 and 12 months after the surgery, and the time required for these was the same as in the initial measurements (1.5-2 hours). Regarding the functional tests, the test scores were not calculated within the testing situation; however, the physiotherapist noted the measurement results on the test form, which were then saved in an electronic format. The results obtained from the tests were compared throughout the study between the patient’s own results and between the intervention and control groups; no comparisons were made with the general reference values of the tests. The knee ROM and swelling, thigh muscle circumference, TUG, stair climbing test, and 6MWT were performed only once. The tests were performed twice only in the static balance test, and the best test result was recorded (the maximum time was 60 seconds).

All the measures of the study are presented in Table 1. During the AlterG training, the weight-bearing symmetry, step length, stance time symmetry, and cadence during walking were measured (Textbox 1).

AlterG measurements.

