## Methods

### Participant Selection and Sampling Strategy

Participants for this RCT study were recruited from two hospitals in the capital region of Finland: Orton Orthopaedic Hospital and Peijas Hospital, both of which are part of the HUS Helsinki University Hospital. Patients with grades 3 and 4 primary knee osteoarthritis and with a scheduled unilateral TKA were included in the study. Those with rheumatoid arthritis, who have undergone hip or knee arthroplasties within the last year, or with a BMI >40 kg/m^2^ were excluded. All eligible patients who came for a knee arthroplasty surgery at Orton Orthopaedic Hospital between 2018 and 2021 and at Peijas Hospital between 2020 and 2021 were asked to participate in the study. The patients were recruited through a nurse’s preoperative visit or a phone call made to the patients attending the surgery. The nurse then checked whether they met the inclusion and exclusion criteria; those who met the criteria were provided with written information regarding the study. The included patients were asked to provide signed consent forms (Multimedia Appendix 1), which they forwarded to the research assistant. When the patient had consented to participate in the trial, the randomization envelope was opened after the surgery. However, due to the nature of the intervention under study (rehabilitation intervention), it was not possible to blind the patients. The patients were randomly allocated either to the treatment group or the control group using a random number generator (StatTrek) by an expert who did not execute the study in practice. All the patients had free access to the available health care services during the study. Overall, 62 patients (31 in each group) were recruited for the study.

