### Data Collection and Statistical Analysis

We estimated that a difference of 30 m in the 6MWT between the two groups would represent a clinically relevant difference [39,40]. To identify such a difference with 2-sided testing (α=.05 and power of 85%), the study required 31 participants in each group, with the assumption of 20% loss to follow-up.

The analysis will use the intention-to-treat principle, which will include all randomized patients. Summary statistics will be described using mean and SD, median and IQR, or numbers and percentages. Statistical comparison between the groups will be performed using the *t* test, Mann-Whitney test, *χ*^2^ test, or Fisher-Freeman-Halton test, as appropriate. A linear mixed model or generalized estimating equation model with appropriate distribution and link function for repeated measurements will be used for analysis. In case of a violation of the test assumptions, a bootstrap-type method or Monte Carlo method will be used. Normal distributions will be graphically evaluated using the Shapiro-Wilk W test. Stata 18 (StataCorp LP) will be used for the analysis. Access to data will be granted to the research team of this study.

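### Three unranked primary outcomes, one with eight dimensions and no primary visit, rest on a sample size built for the 6MWT alone at an undivided two-sided .05

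*Protocol article*

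**What the plan says.** The Abstract, Aims and Objectives, and Outcome Assessment and Measurements all name the same three primary outcomes without ranking them. The last of these ties each to an instrument: "The primary outcomes were walking ability measured with the 6MWT, health-related QoL measured with RAND-36, and perceived pain measured with VAS".

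For RAND-36, the quality-of-life row of Table 1 says "The questionnaire explores well-being and functional ability across eight dimensions". No dimension or summary score is singled out as the primary one.

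On timing, Outcome Assessment and Measurements says "All outcomes were measured before the TKA and 4 and 12 months after the TKA". For the questionnaires it adds a further visit: "In addition to this, the patients were asked to complete the same questionnaires 6-8 weeks after the TKA". So the 6MWT has two postoperative visits, while VAS and RAND-36 have three. No visit is called primary. Aims and Objectives and Expected Findings both predict a group difference that is larger early and fades by 12 months.

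Data Collection and Statistical Analysis sizes the trial on one outcome: "We estimated that a difference of 30 m in the 6MWT between the two groups would represent a clinically relevant difference". The error rate, power and group size follow in the next sentence: "To identify such a difference with 2-sided testing (α=.05 and power of 85%), the study required 31 participants in each group". That number already allows for one patient in five being lost. VAS and RAND-36 get no target difference, SD or power. The same section lists two-group tests and a mixed or GEE model for repeated measurements, without saying which contrast decides the question.

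**The concern.** An outcome is fixed when the variable, the visit and the comparison are fixed. Here the 6MWT and VAS lack a visit, and RAND-36 lacks both a visit and a score. Nothing says whether one, two or all three primaries must succeed for AlterG to be called effective.

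If success on any one of them is enough, the .05 in the sample-size statement is not the error rate of the effectiveness claim. If alpha is later divided, the stated 85% no longer describes the 6MWT test. If all three must succeed, alpha is not inflated, but the joint power is unknown because two of the three outcomes have no power calculation. Under each reading, the three primaries and the sample size do not fit together.

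The predicted time pattern adds to this. An average effect over visits, a 4-month contrast and a 12-month contrast answer different questions when the effect is expected to fade.

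**Working it through.** **Inputs from the article.** Three primaries; eight RAND-36 dimensions; postoperative visits at 4 and 12 months, plus 6-8 weeks for questionnaires; 30 m; two-sided alpha .05; power 85%; 31 per arm; 20% loss.

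**Assumptions.** The SD of the 6MWT and the correlations between test statistics are not stated. The SD is back-solved. Correlation is varied from 0 to 0.7.

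**Step 1: the article's own sample size.** Evaluable per arm: 31 × 0.8 = 24.8, about 25. The normal formula is n = 2(z₁₋α/₂ + z₁₋β)² SD² / δ². Setting n = 25 and δ = 30 gives SD = 30 / [(1.960 + 1.036) × √(2/25)] = 35.4 m. A t-test calculation gives 34.7 m with 25 per arm and 34.5 m with 24.8. With SDs of 34, 35 and 35.4 m, the normal formula followed by division by 0.8 gives 30, 32 and 33 per arm. The figure of 31 is therefore consistent with an SD of about 35 m, but it cannot be confirmed, because no SD is given.

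**Step 2: chance of at least one false positive.** For k independent tests at .05 this is 1 − 0.95^k. For correlated tests, equicorrelated normal test statistics were simulated (300,000 draws).

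| Tests counted | k | Independent | Corr. 0.5 | Corr. 0.7 |
|---|---|---|---|---|
| One per primary outcome | 3 | 14.3% | 12.5% | 11.0% |
| 6MWT, VAS and 8 RAND-36 dimensions, one visit | 10 | 40.1% | 28.6% | 21.3% |
| Those 10 at 4 and 12 months | 20 | 64.2% | 41.8% | 29.1% |
| 6MWT × 2, VAS × 3, 8 dimensions × 3 | 29 | 77.4% | 50.0% | 33.4% |

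The first row needs the fewest assumptions about how the plan is carried out. The other rows apply only if dimensions and visits are tested separately.

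**Step 3: 6MWT power if alpha is shared.** Use SD 34.5 m and 24.8 evaluable per arm. The noncentrality is 30 / [34.5 × √(2/24.8)] = 3.06, with 47.6 degrees of freedom.
- At alpha .05 (critical t 2.01), power is 85%, matching the article.
- At alpha .05/3 = .0167 (critical t 2.48), power is about 72%.

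The normal approximation with 25 per arm and SDs of 34.7-35.4 m gives about 73-75% at alpha .0167. On that basis, keeping 85% at .0167 would need 32-33 evaluable per arm, or 40-42 recruited per arm after 20% loss, against the 31 recruited.

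**The case against.** The strongest reply is that the article never commits to the multiple testing. The .05 appears once, for sizing the 6MWT, and a repeated-measures model can yield one treatment test per outcome. This stands. A reader might infer that every RAND-36 dimension at every visit will be tested at .05, so that success could be claimed on any of 20-29 comparisons and a chance positive is likely. The text does not support that. Those counts are a worst case, and the rate passes one half only with 20 or more separate tests and low correlation.

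A second reply is that multiplicity rules and questionnaire scoring are commonly left to an analysis plan, which is not shown. This also stands, and their absence is not the point. The Table 1 entry describes the instrument and does not establish that the trial will analyse eight scores. What remains is what the article itself fixes: three equal primaries, no primary visit, and a sample size that spends the full .05 on one of them.

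A third reply is that sizing on one outcome is legitimate, and that 85% is claimed only for the 6MWT. That is correct. The fall to about 72% arises only once alpha is shared.

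Finally, reducing the set to a single primary outcome after data collection ended in 2022 could look like outcome switching. That is a fair objection to such a remedy, and the fix below avoids it.

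**Conclusion.** The concern holds in a limited form. Three co-equal primaries, one without a named score and none with a named visit, do not match a sample size calculated for the 6MWT at full alpha. With one unadjusted test per primary, the family-wise error is about 11-14%, more than twice the nominal 5%. It rises to about 29-64% for 20 tests if dimensions and visits are tested separately, which the article leaves open but does not state. The 85% power applies to the 6MWT at alpha .05 only; at .0167 it is about 72%. The error rates rest on assumed correlations of 0 to 0.7, and the power figures on a back-solved SD of about 34.5 m. The 11-14% also presumes that success on any one primary would count as success; the article does not say.

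**What to change.** Before the 2025-26 analysis, and without looking at outcome data by group, record the following in a dated note:

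- **One primary visit.** Four months is the natural candidate: it is the first postoperative visit with a 6MWT, and it fits the hypothesis of an early effect.
- **One named RAND-36 score** as the primary quality-of-life variable. The article gives no basis for preferring a particular one, so the note should give the reason for the choice.
- **Holm across the three named primaries** (6MWT, VAS and the chosen RAND-36 score) at that visit. The smallest p value is compared with .0167, the next with .025 and the last with .05.
- **Other RAND-36 dimensions and other visits** reported as secondary estimates with confidence intervals.
- **Restated power:** about 72% for the 6MWT at the strictest Holm step and 85% only at full alpha, with the SD behind the calculation stated.

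The cost is a short note and a less favourable power figure. Recruitment is closed ("Overall, 62 patients (31 in each group) were recruited for the study"), so the sample size cannot be raised to compensate. Making the 6MWT at 4 months the sole primary is a possible alternative, but it demotes two declared primaries after data collection and is not required.

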**Weight-bearing symmetry**
Weight-bearing symmetry gives information about the symmetry of the stance phase. In pathological situations, the stance phase is shorter on the weaker side [38].
**Step length symmetry**
Step length is the distance from the back of one heel to the back of the other heel [38].
**Stance phase symmetry**
Stance phase is the period when the foot is on the ground [38].
**Cadence (steps/min)**
Cadence is the number of steps taken per minute [38].

### Data Collection and Statistical Analysis

We estimated that a difference of 30 m in the 6MWT between the two groups would represent a clinically relevant difference [39,40]. To identify such a difference with 2-sided testing (α=.05 and power of 85%), the study required 31 participants in each group, with the assumption of 20% loss to follow-up.

The analysis will use the intention-to-treat principle, which will include all randomized patients. Summary statistics will be described using mean and SD, median and IQR, or numbers and percentages. Statistical comparison between the groups will be performed using the *t* test, Mann-Whitney test, *χ*^2^ test, or Fisher-Freeman-Halton test, as appropriate. A linear mixed model or generalized estimating equation model with appropriate distribution and link function for repeated measurements will be used for analysis. In case of a violation of the test assumptions, a bootstrap-type method or Monte Carlo method will be used. Normal distributions will be graphically evaluated using the Shapiro-Wilk W test. Stata 18 (StataCorp LP) will be used for the analysis. Access to data will be granted to the research team of this study.

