### Study Procedure

Patients in both groups underwent initial measurements 1-2 weeks before the surgery, which included questionnaires and functional tests performed by a physiotherapist. All the measurements were taken at Orton Orthopaedic Hospital. First, the patients were asked to complete the questionnaires, and functional tests were then performed. The questionnaires used were a visual analogue scale (measures perceived pain) [20], painDETECT [21], Tampa Scale of Kinesiophobia [22], RAND 36-item Health Survey 1.0 (RAND-36) [23], Oxford Knee Score [24,25], Western Ontario and McMaster Universities Osteoarthritis Index [26], Beck Depression Inventory [27], and State-Trait Anxiety Inventory [28] (Table 1). Functional tests performed were knee range of motion (ROM) [29], knee swelling [30], thigh circumference [31], single-leg stance test [32], Timed Up and Go test (TUG) [33,34], stair climbing test [35], and 6-minute walk test (6MWT) [36] (Table 1).

Patients were asked to complete the same questionnaires 6-8 weeks after surgery. The same questionnaires and functional tests were administered in the same order 4 and 12 months after the surgery at Orton Orthopaedic Hospital. This data can help obtain information regarding short-term (4 months) and long-term (12 months) changes. Then, 6 months after the surgery, the patients were sent a 6-month questionnaire regarding possible rehabilitation sessions, use of medication, and possible complications after TKA. The purpose of this questionnaire was to obtain information regarding their use of health care services and how their rehabilitation and recovery from the surgery have progressed.

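### The group comparisons are named as unadjusted tests, and the repeated-measures model is given no stated role for the baseline values; adjusting for baseline would gain precision at no data cost

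*Protocol article*

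**What the plan says.** The Data Collection and Statistical Analysis section makes two statements about comparing the arms.

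- First, "Statistical comparison between the groups will be performed using the" t test, Mann-Whitney, chi-square or Fisher-Freeman-Halton test, as appropriate. None of these takes a covariate.
- Second, "A linear mixed model or generalized estimating equation model with appropriate distribution and link function for repeated measurements will be used for analysis". No fixed effects are listed. Baseline could be a covariate, one of the repeated outcomes, or left out.

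The article does not say which of the two supplies the treatment effect, and it mentions adjustment for the baseline value nowhere.

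The baseline data are there. Study Procedure states: "Patients in both groups underwent initial measurements 1-2 weeks before the surgery". Outcome Assessment and Measurements confirms that the three primary outcomes (6MWT, RAND-36, VAS) were measured before surgery and again at 4 and 12 months. Participant Selection and Sampling Strategy places the opening of the randomisation envelope after surgery, so the baseline precedes disclosure of the arm.

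On size, the same statistics section says "We estimated that a difference of 30 m in the 6MWT between the two groups would represent a clinically relevant difference" and that "the study required 31 participants in each group, with the assumption of 20% loss to follow-up", at two-sided α of 0.05 and 85% power.

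**The concern.** A pre-allocation measurement of the same outcome usually explains part of the variation at follow-up. A t test on follow-up values discards that information. The estimate then carries whatever chance difference in baseline the randomisation produced, and the confidence interval is wider than it need be. With 62 patients, about 25 per arm after the assumed loss, and no stratification described, this can matter.

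The mixed model does not settle the point as described, because the answer depends on how baseline enters it:

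- As a covariate, or with a common baseline mean, the model recovers the full gain.
- As an unconstrained extra visit with the group-by-visit term as the estimate, it gives a change-score contrast.
- Left out, with the group difference read at the follow-up visit, it gives essentially the raw comparison.

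A second stake is that the article leaves adjusted and unadjusted results both open as the treatment effect, with analysis still to come in 2025 and 2026.

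**Working it through.** **Inputs from the article.** Difference 30 m; two-sided α 0.05; power 85%; 31 per arm ("Overall, 62 patients (31 in each group) were recruited for the study"); 20% loss, so 31 × 0.8 = 24.8, taken as 25 analysed per arm.

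**Inputs not in the article.** The SD of the 6MWT is back-solved below. The baseline to follow-up correlation r is assumed, with a main range of 0.5 to 0.7 and 0.3 as a low case.

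**The plan's own figure.** With no SD stated, 31 cannot be reproduced independently. The SD it implies is

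SD = 30 / [(1.960 + 1.036) × √(2/25)] = 30 / (2.996 × 0.2828) = 35.4 m.

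As a check, SD 35 m needs 2 × 2.996² × 35² / 30² = 24.4 per arm, and 24.4 / 0.8 = 30.6, which rounds up to 31. (Rounding to 25 before inflating gives 32.) An SD of about 35 m is therefore consistent with the plan, but only because it was solved for.

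**Three ways to use the data.** Each has SE = SD × √(f × 2/25) and power = Φ(30/SE − 1.96), with variance factor f:

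- raw follow-up comparison: f = 1
- change from baseline: f = 2(1 − r)
- baseline-adjusted (ANCOVA): f = 1 − r²

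With SD 35.4 m, the raw comparison has SE = 35.4 × 0.2828 = 10.0 m and power 85.0%, whatever r is. The others are:

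| r | Change: SE (m) | Change: power | Adjusted: f | Adjusted: SE (m) | Adjusted: power |
|---|---|---|---|---|---|
| 0.3 | 11.9 | 71.6% | 0.91 | 9.6 | 88.1% |
| 0.5 | 10.0 | 85.0% | 0.75 | 8.7 | 93.3% |
| 0.6 | 9.0 | 91.8% | 0.64 | 8.0 | 96.3% |
| 0.7 | 7.8 | 97.2% | 0.51 | 7.2 | 98.7% |

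In 95% CI half-widths (1.96 × SE), the raw comparison gives about 19.6 m. The adjusted one gives about 17.0, 15.7 and 14.0 m at r = 0.5, 0.6 and 0.7.

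**Adjusted against change score.** The ratio of variances is (1 − r²) / [2(1 − r)] = (1 + r)/2, that is 0.75, 0.80 and 0.85. The saving is 25%, 20% and 15%, smaller than the 25%, 36% and 49% saved against the raw comparison.

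**Sensitivity to the SD.** If the SD of follow-up values were 60 m (an assumption), power at 25 per arm would be 42% raw. At r = 0.5, 0.6 and 0.7 it would be 42%, 51% and 63% for change, and 53%, 60% and 70% adjusted.

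**Sensitivity to what the SD describes.** If 35.4 m were instead the SD of change, the change-score analysis would have 85% power and the adjusted analysis 93%, 92% and 90% at r = 0.5, 0.6 and 0.7.

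**The case against.** The strongest reply is that the article is silent on the model's terms, and silence is not a decision to omit baseline. That stands. A reader might infer that the planned mixed model has no baseline term, or that it is a change-score analysis. The text supports neither: it lists no terms at all, and is equally compatible with the adjustment proposed here. A fuller analysis plan, not shown, may specify it. What remains is that covariate-free tests are positively named for comparing the groups, and nothing says they are secondary to the model.

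A reader might also infer that the plan gains 8 to 14 percentage points of power whatever the model. That gain is measured against a raw follow-up test only. Against a change-score contrast it is about 8, 4.5 and 1.5 points at r = 0.5, 0.6 and 0.7.

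Nor should one infer bias. Under randomisation the unadjusted comparison is valid, and chance imbalance costs precision, not validity. In a change-score analysis the baseline is subtracted, so imbalance does not pass straight into the estimate as it does in the raw comparison.

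Finally, neither the SD nor r is in the article, and nothing says whether the implied 35 m describes follow-up values, changes or residuals. That limits how firmly the gain can be quantified. It does not reverse its direction: 1 − r² is never larger than 1 or 2(1 − r), apart from the small cost of estimating one slope.

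**Conclusion.** The concern holds as an avoidable loss of efficiency of uncertain size, together with an unresolved choice of treatment-effect analysis. It is not an error that invalidates the trial.

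On the stated design, with SD about 35 m taken as the SD of follow-up values and 25 analysed per arm, baseline adjustment would give about 93%, 96% and 99% power at r = 0.5, 0.6 and 0.7. The raw follow-up comparison gives 85%, and a change-score contrast 85%, 92% and 97%. Below r = 0.5 the change score is worse than ignoring baseline, while adjustment still helps. The arithmetic covers the 6MWT only. The same reasoning applies to RAND-36 and VAS, but the article gives no figures from which to size it.

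**What to change.** For each continuous outcome, state that the treatment effect comes from one mixed model on the post-surgery visits, with group, visit, group × visit, and the baseline value of that outcome with its interaction with visit. Equivalently, include baseline as an outcome with its mean constrained equal between arms. The visits would be 4 and 12 months for the 6MWT, and 6-8 weeks, 4 and 12 months for VAS and RAND-36. Report the adjusted mean difference at each visit with its 95% CI. Keep the t and Mann-Whitney tests as descriptive or supportive only.

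The cost is a sentence or two in the analysis plan and one baseline covariate (with its visit interaction) per model. No new data are needed. The rule should be fixed and dated before outcomes are compared by group, so that adjusted and unadjusted results cannot be chosen between afterwards.
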